### Exit criteria corresponding to treatment failure

•Uncontrolled blood pressure.

•HbA1C levels >59 mmol/mol.

•Uncontrolled blood glucose.

•Persistently elevated proteinuria.

### Interventions

Participants randomized to the treatment group will be administered SYKFT 2.4 g three times daily plus irbesartan 0.15 g once daily for 16 weeks. Those in the control group will receive SYKFT placebo 2.4 g three times daily in addition to irbesartan 0.15 g once daily for 16 weeks. Both groups will receive behavioral intervention and health education such as diet instructions. All test drugs, that is SYKFT, the placebo and irbesartan (trade name: Anbowei in Chinese pinyin) are manufactured by Tianjin Tongrentang Pharmaceuticals.

### Measurement items and time points of data collection

Relevant examinations will be performed and patient data will be collected at 2 weeks before baseline, at baseline, at 2 weeks post baseline and every 4 weeks from 4 to 16 weeks during treatment. Items to be measured and the time points of data collection can be found in Table 1.

**Table 1 T1:** Measurement items and point of data capture

	**Screening**	**Baseline**	**Treatment**				
	**Visit 1**	**Visit 2**	**Visit 3**	**Visit 4**	**Visit 5**	**Visit 6**	**Visit 7**
**Items**	**−2 weeks**	**0 weeks**	**2 weeks**	**4 weeks**	**8 weeks**	**12 weeks**	**16 weeks**
Informed consent form	X						
Inclusion/exclusion criteria	X						
Demographic information	X						
Medical/drug use history	X						
Concomitant disease and treatment	X						
General physical examination	X						
Combined medication	X	X	X	X	X	X	X
Vital signs	X	X	X	X	X	X	X
TCM symptom	X	X	X	X	X	X	X
Urine protein test	X	X	X	X	X	X	X
Routine urine test	X	X	X	X	X	X	X
Renal function (SCR, BUN, GFR) Serum albumin	X	X	X				X
Routine blood test	X	X					X
Stool routine test and fecal occult blood test	X	X					X
Liver function (ALT/AST/GGT/TBIL/ALB)	X	X					X
Blood electrolytes	X	X	X				X
Blood coagulation (TT/APTT/PT/FIB)	X	X					X
Blood glucose	X	X	X	X	X	X	X
Glycosylated hemoglobin	X	X			X		
Electrocardiogram (EGG)	X	X					X
Adverse events	X	X	X	X	X	X	X
Randomization		X					
Drug distribution	X	X	X	X	X	X	
Drug recycling		X	X	X	X	X	X
Drug count		X	X	X	X	X	X
Research conclusion							X

X: Have indicators tested in the specific time period. ALB, serum albumin; ALT, alanine aminotransferase; APTT, activated partial thromboplastin time; AST, aspartate aminotransferase; BUN, blood urea nitrogen; FIB, fibrinogen; GFR, glomerular filtration rate; GGT, gamma-glutamyl transpeptidase; PT, prothrombin time; SCR, serum creatinine; TBIL, total bilirubin; TCM, traditional Chinese medicine; TT, thrombin time.

### Outcome measurements

#### Primary outcomes

The primary outcome of this trial will be the composite of the quantitative 24-hour urinary protein levels and urinary albumin excretion rate (UAER).

#### Secondary outcomes

Secondary outcomes include changes in urine albumin-to-creatinine ratio (UACR), TCM symptom improvement and changes in diabetic nephropathy staging (for example, from phase III to IV).

#### Safety outcomes

Adverse events will be monitored throughout the trial and several biological indicators (routine blood and urine test, stool routine test, electrocardiogram (ECG), liver function and blood coagulation) will also be closely watched.

### Measurement tools

#### Measurement scale for TCM symptoms

The measurement scale for TCM symptoms recommended by the Guidelines for Clinical Research of Chinese Medicine (New Drug) [9] will be used for ease of assessment. Each of the primary symptoms necessary for the diagnosis of qi-yin deficiency syndrome will be scored 0, 2, 4 or 6, while a secondary symptom is scored 0, 1, 2 or 3, and the scores then summed to yield a total score of both types of symptoms for a patient. It is stipulated that the total primary symptom score shall not exceed 18, and the total score for secondary symptoms shall not exceed 33 for an individual patient.

### Efficacy assessment tools

#### For TCM symptoms

Following the Guidelines for Clinical Research of Chinese Medicine (New Drug) [9], the reduction in the total TCM symptom score of the patient will be calculated and used as an efficacy indicator (EI) for the evaluation of treatment efficacy. EIs will be calculated according to the following formula:

$$\begin{array}{l} \mathrm{EI}=\left(\mathrm{Total}\;\mathrm{symptom}\;\mathrm{score}\;\mathrm{at}\;\mathrm{baseline}\right)\\ \left(\;-\mathrm{Total}\;\mathrm{symptom}\;\mathrm{score}\;\mathrm{post}\;\mathrm{treatment}\right)/\\ \;\mathrm{Total}\;\mathrm{symptom}\;\mathrm{score}\;\mathrm{at}\;\mathrm{baseline}\times 100\% \end{array}$$

The degree of symptom improvement will be presented in four categories ranging from ‘full recovery’ (EI ≥90%), ‘good recovery’ (90% >EI ≥70%), ‘modest recovery’ (70% >EI ≥30%) to ‘no recovery’ (EI <30%).

### For laboratory indicators of the disease

Full recovery (FR): the quantitative 24-hour urinary protein, UAER and renal function return to normal levels.

Good recovery (GR): a decrease of ≥40% in UAER or the quantitative 24-hour urinary protein.

Modest recovery (MR): a decrease of <40% in UAER or the quantitative 24-hour urinary protein.

No recovery (NR): unchanged or worsened laboratory test results.

To assess efficacy with regard to either TCM symptom improvement or amelioration of clinical signs, an overall recovery rate (ORR) will be calculated using the following formula.

$$\begin{array}{l} \mathrm{ORR}=\left(\mathrm{FR}\;\mathrm{count}+\mathrm{GR}\;\mathrm{count}+\mathrm{MR}\;\mathrm{count}\right)/\\ \;\mathrm{Group}\;\mathrm{population}\times 100\%. \end{array}$$

### Reporting of adverse events

Adverse events (AEs) will be recorded in medical diagnostic terminology. Detailed symptoms, time of occurrence, duration, severity, possible causal relationships, actions taken, results and other relevant information will be reported. In the case of an adverse event, researchers must fill out a serious adverse event (SAE) form and notify both the institutional review board (IRB) and the regulatory authorities within 24 hours.

### Sample size calculation

This is an exploratory phase II clinical study designed to provide evidence and a scientific rationale for advancing the treatment regimen into a phase III confirmatory study. The planned sample size is 80, with 40 in each treatment group.

### Randomization and allocation concealment

A total of 80 patients will be randomly assigned in a ratio of 1:1 to either the SI or the PI group using a computer-generated random number sequence. To guarantee rigorous methodology, center-stratified randomization and central coordination will be initiated. The central randomization system will assign a unique code to each newly included participant, who will then be administered the corresponding treatment regimen.

An expert statistician of the Tianjin Institute of Clinical Evaluation and a staff member from the sponsoring organization will act as the coder, and they will be shielded from patient recruitment. The trial management board will be responsible for keeping the blinding codes and other information confidential.

### Blinding

This trial will use the double-blind design. The placebo tablets are indistinguishable from SYKFT in shape, size, color and packaging. Thus, both participants and clinicians will be masked. Moreover, a designated pharmacist not involved with the study will be held responsible for handing out medication.

### Statistical analysis

The statistical analysis will be performed by a statistician with the Tianjin Institute of Clinical Evaluation, and the data will be analyzed using Statistical Analysis System (SAS) software version 9.2 (SAS Institute Inc., Cary, NC, USA). A formal and detailed statistical analysis plan will be documented prior to data locking.

### Efficacy assessment

All primary analyses for this study will strictly follow the intention-to-treat (ITT) principle. The full analysis set (FAS) population, which will include randomized subjects who have received treatment at least once, will be used for primary efficacy outcomes analysis. In addition, a per-protocol analysis will be performed on the secondary outcomes. The per-protocol set (PPS) population will be restricted to patients who are compliant with the treatment protocol and have a completed CRF. Good compliance indicates the drug actually taken equals 80 to 120 percent of the required dosage. Missing values will be replaced using the last observation carried forward (LOCF) method.

Continuous variables will be described as mean ± standard deviation, and dichotomous data will be reported as percentages. A two-tailed test will be applied. Statistical significance will be defined as *P* <0.05 and 95% confidence interval will be calculated. Heterogeneity between groups will be tested at baseline.

The main analysis will be a comparison between the two groups concerning the proportion of patients achieving different levels of recovery (FR, GR, MR or NR) in terms of TCM symptoms and clinical biomarkers using the Wilcoxon rank sum test. In addition, the ORR will be compared between the two arms using the center-stratified Cochran-Mantel-Haenszel (CMH) method. For secondary outcomes, all continuous data will be analyzed via analysis of covariance adjusted for clinical center and baseline. Analyses of binary data will be based on logistic regression models.

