### Study criteria

#### Diagnostic criteria

##### Diagnostic criteria for DN

Stage III: early-stage diabetic nephropathy. Urinary albumin excretion rate (UAER) falls within the range of 20 to 200 ug/min or 30 to 300 mg/24h, accompanied by slightly elevated blood pressure.

Stage IV: also termed clinical or dominant diabetic nephropathy. This stage is featured by a large amount of proteinuria, UAER >200 ug/min or the urinary protein quantitative is persistently higher than 500 mg/24h, and it is nonselective proteinuria. Some may present elevated blood pressure and symptoms of nephrotic syndrome.

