#### Exclusion criteria

•Diagnosis of kidney cancer or other types of renal damage.

•Presence of complications that might affect observation on the curative effects of the test drug.

•Uncontrolled hypertension (blood pressure being persistently greater than 140/90 mmHg).

•Diagnosis of type 1 diabetes mellitus.

•Presence of urinary tract infection.

•Glycated hemoglobin (HbA1c) >59 mmol/mol.

•Twenty-four-hour urinary protein >3 g, serum albumin (ALB) <25 g/L and glomerular filtration rate (GFR) <60 ml/min.

•Presence of serious primary hepatic, pulmonary, hematologic or cardiovascular diseases or any other life-threatening conditions.

•History of allergy to TCM products.

•Recent participation in another clinical trial.

•Pregnancy, lactation or those who are preparing for pregnancy.

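### LOCF is applied without exception to treatment-failure exits, and no rule scores them as no recovery, so a declared failure can count as recovered

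*Protocol article*

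**What the plan says.** All references are to the protocol article.

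- **Failure exits.** A section headed "Exit criteria corresponding to treatment failure" lists four reasons: uncontrolled blood pressure, HbA1c above 59 mmol/mol, uncontrolled blood glucose, and "Persistently elevated proteinuria". The last has no threshold and no reference value.
- **Analysis set and missing data.** Under Efficacy assessment, the full analysis set (FAS) consists of "randomized subjects who have received treatment at least once", so patients who exit stay in. The same paragraph says "Missing values will be replaced using the last observation carried forward (LOCF) method", without exception.
- **Laboratory categories.** In the section on laboratory indicators of the disease, good recovery (GR) is a fall of at least 40% in either marker. Modest recovery (MR) is "a decrease of <40% in UAER or the quantitative 24-hour urinary protein". No recovery (NR) covers only results that are unchanged or worse.
- **TCM categories.** In the section on TCM symptoms, recovery depends only on the symptom score: a reduction of 30% or more is at least modest recovery.
- **Use.** The ORR counts full recovery (FR), GR and MR over the group population. The main analysis is a Wilcoxon rank sum test on the four categories. The ORR is also compared by a center-stratified CMH test.

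**The concern.** The protocol gives two verdicts on the same patient. The exit section says that treatment has failed. The analysis section then carries forward that patient's last value and grades it by change from baseline, with nothing that sends a failure exit to NR. If the last value was below baseline, the declared failure enters the main analysis as MR or GR and adds to the ORR numerator.

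The Sample size calculation section says the trial is exploratory and is meant to support a phase III study. With 40 patients per arm, each rescored patient moves that arm's ORR by 1/40 = 2.5 points, so a few such patients can change the response level, and possibly the contrast, that the next trial is planned on.

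**Working it through.** The plan gives no exit rate and no expected ORR, so there is no figure to reproduce. The check applies the stated rules first and then shows a range under stated assumptions.

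**1. Is there a value to carry forward?** Table 1 schedules the item "Urine protein test" and the TCM symptom assessment at every visit, at weeks 0, 2, 4, 8, 12 and 16 after screening. An exit at any post-baseline visit therefore leaves an on-treatment value. An exit before the first such visit carries the baseline value, which is unchanged and so NR.

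**2. Can a proteinuria exit be graded as recovered on laboratory markers?** This depends on what persistently elevated means.

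- *Judged as a level.* Assume 500 mg/24h, borrowed from the stage IV diagnostic criterion ("the urinary protein quantitative is persistently higher than 500 mg/24h").
  - Baseline 1,000, last value 950: fall = 50/1,000 = 5%, graded MR, still above 500.
  - Baseline 1,000, last value 600: fall = 400/1,000 = 40%, graded GR, still above 500.
  - A patient can be GR and still elevated whenever baseline exceeds 500/0.6 = 833 mg/24h.
- *Judged as no fall from the patient's own baseline on either marker.* The carried value is then unchanged or worse, and the laboratory grade is already NR. The TCM grade can still be recovery, because it ignores proteinuria.

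**3. The other three exits.** Blood pressure, HbA1c and glucose exits say nothing about urine protein. A carried-forward protein fall is graded MR or GR, and it may be real. The conflict there rests on the protocol's own failure label.

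**4. How easily does a fall arise?** A fall in either marker is enough. If neither marker truly changes and the two changes are bivariate normal with correlation ρ, P(at least one falls) = 1 − [1/4 + arcsin(ρ)/(2π)]. This is 75% at ρ = 0, 67% at 0.5, 60% at 0.8 and 57% at 0.9. Patients selected for exit because of high protein would have a lower chance, so the range used below is 25% to 75%.

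**5. Effect on the ORR level of one arm**, relative to scoring exits as NR: exit rate × chance of a carried-forward fall. The exit rates are assumptions that pool all four criteria. They are kept low because entry already bars uncontrolled hypertension and HbA1c above 59 mmol/mol.

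| Exits of 40 | Rate | Rise in ORR (points) |
|---|---|---|
| 2 | 5% | 1.25 to 3.75 |
| 4 | 10% | 2.5 to 7.5 |
| 6 | 15% | 3.75 to 11.25 |

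**6. Effect on the contrast**, first-named arm minus second: e1·p1 − e2·p2, with p1 and p2 each between 0.25 and 0.75.

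- 4 v 4 exits: 0 if p1 = p2; otherwise from 10×0.25 − 10×0.75 = −5 to +5 points.
- 4 v 2 exits: from 10×0.25 − 5×0.75 = −1.25 to 10×0.75 − 5×0.25 = +6.25 points.
- 6 v 2 exits: from 15×0.25 − 5×0.75 = 0 to 15×0.75 − 5×0.25 = +10 points.

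**7. Scale.** At an assumed ORR of 70% in both arms, the standard error of the difference is √(2×0.7×0.3/40) = 10.2 points (11.0 at 60%, 8.9 at 80%). The largest shifts in step 6 are 5/10.2 = 0.49, 6.25/10.2 = 0.61 and 10/10.2 = 0.98 standard errors. At an ORR of 80% the last is 10/8.9 = 1.12.

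**The case against.** **The threshold is borrowed.** The exit criterion has no level, and 500 mg/24h fits it poorly. Stage IV patients are eligible, so anyone who qualified on that criterion would already be above it at randomization. A reading relative to baseline is at least as natural, and under it the laboratory conflict for proteinuria exits goes away. This stands. A reader might infer that every proteinuria exit is bound to be miscounted, or that the two sections flatly contradict each other. The text does not support that. It supports only that the stated rules permit the outcome, on one reading for laboratory grades and on any reading for TCM grades.

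**The GR example is unlikely.** An investigator would have to exit a patient for proteinuria after a fall that the protocol itself calls good recovery. This is fair as to frequency. The example's use is to show that a lower bound on MR would not by itself remove the conflict.

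**LOCF is not the cause.** A completer who moves from 1,000 to 950 mg/24h is also graded MR. That is true, and the missing lower bound on MR is a separate matter. But the completer has not been declared a treatment failure. The fault lies in LOCF combined with the absence of a failure rule.

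**For three of the four exits, NR is a choice.** This stands too. The primary outcome is urinary protein and UAER, and a fall there may be genuine when the exit is for blood pressure or glycaemia. NR follows the protocol's label but is not the only defensible scoring.

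**The SAP may deal with it.** The article foresees a detailed plan before data lock, and that plan may hold an exception. However, the article already fixes LOCF and the categories, and a plan that follows it as written reproduces the problem.

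**Conclusion.** The point holds as a defect in a stated rule. LOCF covers patients whom the protocol calls treatment failures, and nothing scores them as NR, so such a patient can count as recovered in the laboratory or TCM category analysis and in the ORR. For proteinuria exits, the laboratory part depends on an undefined term being read as a level.

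Size and direction are unknown. Under assumed exit rates of 5% to 15% and a 25% to 75% chance of a carried-forward fall, an arm's ORR rises by 1.25 to 11.25 points. Both assumptions pool the four exit types, and the documents support neither. The contrast does not move if exits and chances are equal across arms. In the scenarios shown it moves by −5 to +10 points, about one standard error at most.

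A reader might infer that the rule favours the SYKFT arm or inflates the treatment effect. The documents give no basis for this: the shift can go either way, and the arm with more exits need not gain more. The figures are gaps between two scoring rules, not bias from a known truth. The point is worth fixing before data lock, but it does not threaten the trial.

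**What to change.** - In the category and ORR analyses, score every exit under the treatment-failure criteria as NR, whatever the last value. This point asks for no change to LOCF for other missing data.
- Repeat these analyses with LOCF scoring of all such exits as a sensitivity analysis.
- Tabulate failure exits by arm and criterion, so that blood pressure, HbA1c and glucose exits with a real protein fall can be told from proteinuria exits.

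This costs one scoring sentence, one sensitivity analysis and one table, with no new data. The downside is a somewhat lower ORR (2.5 to 7.5 points in an arm with 10% exits, under the assumptions above). Some blood pressure or glycaemic exits with a genuine protein fall will also be counted as NR; the sensitivity analysis shows how much that matters.

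### The main analysis tests TCM symptoms alongside the laboratory outcome, although the outcome sections make the urine composite the only primary outcome and TCM symptoms secondary

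*Protocol article*

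**What the plan says.** The outcome sections of the protocol article are clear and agree with its Abstract. On what is primary, the article states: "The primary outcome of this trial will be the composite of the quantitative 24-hour urinary protein levels and urinary albumin excretion rate (UAER". TCM symptoms are placed one tier lower, under the next heading: "Secondary outcomes include changes in urine albumin-to-creatinine ratio (UACR), TCM symptom improvement and changes in diabetic nephropathy staging".

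The Efficacy assessment section (under Statistical analysis) sets out the tests. Its main analysis compares the arms on level of recovery, "FR, GR, MR or NR) in terms of TCM symptoms and clinical biomarkers using the Wilcoxon rank sum test". It continues: "In addition, the ORR will be compared between the two arms using the center-stratified Cochran-Mantel-Haenszel (CMH) method". The methods for secondary outcomes come after that, in sentences of their own (covariance analysis for continuous data, logistic regression for binary data). One significance rule covers everything: "A two-tailed test will be applied" and "Statistical significance will be defined as *P* <0.05 and 95% confidence interval will be calculated".

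The section on laboratory indicators shows that there is an ORR for each domain: "To assess efficacy with regard to either TCM symptom improvement or amelioration of clinical signs, an overall recovery rate (ORR) will be calculated".

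On status, the Sample size calculation section calls the study exploratory phase II, while the Objectives section asks whether the SI regimen is superior to PI.

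**The concern.** The two parts of the article rank TCM symptoms differently. Under the outcome headings they are secondary. In the analysis section they stand beside the laboratory outcome in the main analysis, which that section sets apart from the secondary outcomes. Nothing else in the analysis section tests the urine composite, so the main analysis cannot be read as a general remark on methods that leaves the primary test to another sentence.

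Three things are at stake.

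- **Reporting.** If the symptom comparison is significant and the laboratory comparison is not, the article supports two accounts: the primary outcome failed, or one of the two main tests succeeded. The symptom score is a clinical rating and the urine measures are laboratory values, so these would be quite different claims for the regimen.
- **Error rate.** Two main tests at 0.05 each do not give a 5% chance of a false-positive main result.
- **Analysis set.** The full analysis set serves the primary outcomes, and a per-protocol analysis is added for the secondary ones. TCM symptoms fit both descriptions.

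**Working it through.** **Inputs**

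- Significance level 0.05, two-sided, with no split between tests (Efficacy assessment).
- Two domains in the main analysis, each with a Wilcoxon test (Efficacy assessment).
- One ORR per domain (laboratory indicators section), compared by CMH (Efficacy assessment). This makes two further tests, introduced as additions.
- 40 patients per arm: "The planned sample size is 80, with 40 in each treatment group".

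The article gives no overall error rate to reproduce; 0.05 per test is its only figure. The sample size cannot be re-derived either, because no effect size, variability or power is stated. It is used below only to set the arm sizes.

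**Step 1: the two Wilcoxon tests, independent, no effect in either domain**

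- At least one significant: 1 − (1 − 0.05)² = 1 − 0.9025 = 0.0975.
- Symptoms significant and laboratory not: 0.05 × 0.95 = 0.0475.
- Laboratory significant and symptoms not: 0.95 × 0.05 = 0.0475.
- Both significant: 0.05 × 0.05 = 0.0025.
- Check: 0.0475 + 0.0475 + 0.0025 = 0.0975.

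Nearly half of the false-positive main results would therefore be symptom-only. Counting only results that favour SI, the figure is 1 − 0.975² = 0.0494 against 0.025, so the rate again roughly doubles.

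**Step 2: the same two tests, simulated**

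The simulation used 8,000 null trials per scenario, 40 against 40, and a tie-corrected Wilcoxon test on the four-level scale. The following are assumptions, not figures from the article:

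- five equal centres of 16 patients;
- three category distributions, with no recovery at 25%, 30% or 50%;
- latent correlation between domains of 0, 0.3 or 0.6.

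Over the nine scenarios, the chance of at least one significant Wilcoxon test was 8.8% to 9.8%. The Monte Carlo standard error is about √(0.0975 × 0.9025 / 8,000) = 0.0033, so correlation between the domains lowers the rate only slightly.

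**Step 3: if both ORR comparisons also counted as deciding**

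- Four independent tests: 1 − 0.95⁴ = 0.1855. The upper bound is 4 × 0.05 = 0.20.
- Each ORR collapses the same four-level scale into recovery or none, so the tests overlap. In the same simulation, with the CMH test stratified by centre, at least one of four was significant in 12.7% to 15.3% of trials.
- Using both methods within a single domain gave 6.8% to 8.3%.

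**Step 4: after the repair**

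One designated test at two-sided 0.05 returns the rate to 5%.

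**The case against.** **Exploratory study.** The article presents the trial as preparation for a phase III confirmatory study, so strict control of the overall error rate matters less. This stands, and it lowers the severity. It does not reconcile the outcome sections with the analysis section. The Objectives section also speaks of superiority, and a decision to go on to phase III still needs to know which result it rests on.

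**Left to the analysis plan.** A detailed plan is promised before data lock, and test order and error allocation commonly belong there. Their absence from an article is no defect, and this point does not rest on it. It rests on two statements already made in the article, one of which a later plan would have to overrule.

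**The ranking can be inferred.** Read together, the sections leave the laboratory Wilcoxon test as the only one that is both on the primary outcome and in the main analysis. That is a sensible reading and the one the fix adopts. But the reader has to construct it, against the plain wording of the analysis section.

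**A stronger reading.** A reader might count two domains by two methods and infer four deciding tests of equal rank, with an error rate of 18.5% or more. The documents do not support this. The ORR comparison is introduced as an addition to the main analysis, which places it after the Wilcoxon test, and the tests within a domain share one scale and so are far from independent. The Abstract does mention ORR first among the effects to be assessed, so its supportive status is worth stating, but that does not make it co-main.

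**Conclusion.** The contradiction is real and of moderate severity. The outcome sections make the urine composite the sole primary outcome, and the analysis section gives TCM symptoms equal place in the main analysis at the same threshold.

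Followed as written, the chance of at least one false-positive main test is about 9–10% rather than 5%. The 9.75% figure assumes independence between domains; the simulated 8.8–9.8% allows for correlation. The 13–15% figure holds only if both ORR comparisons are treated as deciding, and only under the assumed category distributions, correlations and centre sizes.

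These rates describe the case of no effect in either domain. If the regimen improves symptoms but not urine protein, the chance of a symptom-only main finding depends on the power of the symptom test, which cannot be worked out from the article.

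**What to change.** In the Efficacy assessment section, restrict the main analysis to the Wilcoxon comparison of the laboratory recovery categories (24-hour urinary protein and UAER), in the full analysis set, at two-sided 0.05. State that the TCM symptom categories are a secondary analysis and that both ORR comparisons, laboratory and symptom, are supportive, all with nominal p-values. This matches the outcome sections and settles which analysis set applies to TCM symptoms.

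The Wilcoxon test stays as specified, since nothing in this point calls for a different method. The change does not settle how a patient is graded when UAER and 24-hour protein fall by different amounts; that lies in the category definitions and needs separate attention.

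The cost is a change of wording and the loss of co-main status for the TCM symptom result. No data collection or sample size changes. The amendment should be dated and made before unblinding; the Trial status section reports 20 patients randomised by March 2013.

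### The main efficacy test cuts two continuous urine markers into four categories and compares them with an unstratified, unadjusted Wilcoxon test, at a cost in power and with no effect estimate on the marker scale

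*Protocol article*

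**What the plan says.** All references are to the protocol article.

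- **Primary outcomes:** "The primary outcome of this trial will be the composite of the quantitative 24-hour urinary protein levels and urinary albumin excretion rate (UAER"). Both components are measured on a continuous scale.
- **For laboratory indicators of the disease:** the markers become four levels. Full recovery (FR) requires both markers and renal function to be normal. Good recovery (GR) is "a decrease of ≥40% in UAER or the quantitative 24-hour urinary protein". Modest recovery (MR) is "a decrease of <40% in UAER or the quantitative 24-hour urinary protein". No recovery (NR) is "unchanged or worsened laboratory test results".
- **Efficacy assessment:** the main analysis compares the arms on the four recovery levels, and the test is given as "in terms of TCM symptoms and clinical biomarkers using the Wilcoxon rank sum test". No centre term or covariate is named. The overall recovery rate (ORR: FR, GR and MR against NR) is additionally compared with a CMH test stratified by centre.
- **Same section:** "For secondary outcomes, all continuous data will be analyzed via analysis of covariance adjusted for clinical center and baseline". Change in the urine albumin-to-creatinine ratio (UACR) is one of these outcomes.
- **Randomization and allocation concealment:** "center-stratified randomization and central coordination will be initiated". The Setting section lists five sites.

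The article states no analysis of UAER or 24-hour protein as continuous values.

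**The concern.** Albuminuria is analysed in two ways. As a secondary outcome (UACR) it stays continuous and is adjusted for centre and baseline. As part of the primary outcome (UAER) it is categorised and compared without either term. The article gives no reason for the difference. This is not a detail left to the analysis plan, because the article itself names the test and calls it the main analysis.

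Two things are at stake. The first is power in a trial of 80 patients. The second is usefulness: the Sample size calculation section says the study is meant to support a phase III trial. Planning that trial needs the size of the effect on the markers and its precision. A rank test on four categories gives a P value, and the CMH analysis can at best describe the proportion with any recovery. Neither says by how much the markers fell.

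**Working it through.** **1. What the categories discard.** On the log scale, a 39% fall is ln 0.61 = -0.494 and a 40% fall is ln 0.60 = -0.511. They differ by 0.017 but fall in different categories (MR and GR). An 80% fall is ln 0.20 = -1.609. It differs from the 40% fall by 1.099 but shares its category (GR) unless the values normalise.

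**2. Inputs from the article.** 80 patients, 40 per arm, five centres, centre-stratified 1:1 randomisation, two-sided 0.05, and the category cut-offs above. The sample size of 80 cannot be reproduced, because no effect, SD or power is given with it.

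**3. Assumptions, none of them in the article.** One log-normal marker (UAER); baseline median 250 mg/24h, log-SD 1.0, limited to 30 to 2,500; normal below 30 mg/24h; control change ×0.85; treatment ratio 0.70 or 0.65; residual log-SD 0.5 or 0.7; centre log-SD 0 or 0.3; slope on log baseline (b) 1.0 or 0.8; 16 patients per centre; 2,000 trials per scenario.

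Model: ln y = ln 250 + b(ln x − ln 250) + ln 0.85 + arm × ln(ratio) + centre + error, where x is baseline and y is follow-up.

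**4. Tests compared.**
- Planned Wilcoxon on the four levels: Z = (W − m(N+1)/2) / √[m(N−m)/(N(N−1)) × Σ(rᵢ − r̄)²]. With N = 80 and m = 40, the expected rank sum is 40 × 81/2 = 1,620.
- van Elteren: the same categories ranked within centre, with weight 1/(n+1) per centre.
- CMH on ORR, stratified by centre.
- ANCOVA: ln y on arm, ln x and centre.

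**5. Power (%).**

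| Ratio | Resid. SD | Centre SD | b | Wilcoxon | van Elteren | CMH ORR | ANCOVA | ANCOVA − Wilcoxon |
|---|---|---|---|---|---|---|---|---|
| 0.70 | 0.5 | 0 | 1.0 | 79.3 | 78.5 | 63.8 | 89.2 | 9.9 |
| 0.70 | 0.5 | 0 | 0.8 | 75.7 | 75.0 | 60.1 | 87.6 | 11.9 |
| 0.70 | 0.5 | 0.3 | 1.0 | 68.2 | 74.2 | 58.6 | 88.0 | 19.8 |
| 0.70 | 0.5 | 0.3 | 0.8 | 66.7 | 72.3 | 55.2 | 88.7 | 22.0 |
| 0.70 | 0.7 | 0 | 1.0 | 50.1 | 49.5 | 39.4 | 60.5 | 10.4 |
| 0.70 | 0.7 | 0 | 0.8 | 49.4 | 49.4 | 37.8 | 60.6 | 11.2 |
| 0.70 | 0.7 | 0.3 | 1.0 | 44.7 | 48.6 | 36.9 | 60.1 | 15.4 |
| 0.70 | 0.7 | 0.3 | 0.8 | 41.6 | 45.8 | 35.4 | 60.8 | 19.2 |
| 0.65 | 0.5 | 0 | 1.0 | 90.4 | 90.2 | 78.1 | 96.6 | 6.2 |
| 0.65 | 0.5 | 0 | 0.8 | 89.7 | 88.8 | 74.1 | 97.5 | 7.8 |
| 0.65 | 0.5 | 0.3 | 1.0 | 84.0 | 87.9 | 72.8 | 97.0 | 13.0 |
| 0.65 | 0.5 | 0.3 | 0.8 | 82.7 | 86.4 | 70.8 | 97.0 | 14.3 |
| 0.65 | 0.7 | 0 | 1.0 | 64.4 | 64.2 | 54.8 | 76.0 | 11.6 |
| 0.65 | 0.7 | 0 | 0.8 | 62.8 | 62.8 | 50.6 | 75.6 | 12.8 |
| 0.65 | 0.7 | 0.3 | 1.0 | 60.4 | 63.2 | 53.4 | 78.0 | 17.6 |
| 0.65 | 0.7 | 0.3 | 0.8 | 59.2 | 61.8 | 47.6 | 77.9 | 18.7 |

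The gain from ANCOVA is 6.2 to 22.0 points. Stratifying the category test gains 2.6 to 6.0 points when centres differ and nothing when they do not. CMH on ORR is below the Wilcoxon in every row.

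**6. Where the loss arises.** A Wilcoxon test on the uncategorised log change had 75.5% power in row 4. Categorising therefore costs 75.5 − 66.7 = 8.8 points, and the remaining 88.7 − 75.5 = 13.2 come with the adjusted model. In row 1 it had 88.2%, so the split is 8.9 and 1.0.

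**7. Type I error.** With no treatment effect and centre SD 0.3, the Wilcoxon rejected in 2.6 to 4.0% of trials and ANCOVA in 4.6 to 5.5%. With no centre differences the Wilcoxon rejected in 4.8 to 6.0%. The simulation error is √(0.05 × 0.95/2,000) = 0.5 points, so this is compatible with 5%.

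**8. A second simulation with both markers.** It assumed marker correlation 0.5, a 25% fall in both arms and a further 25% on the study drug, with categories set by the better marker and FR not modelled; 1,500 trials per setting. For SD of log change 0.4 / 0.55 / 0.7, power was 79 / 56 / 35% for the category Wilcoxon, 91 / 69 / 48% for ANCOVA on log UAER, and 96 / 81 / 59% for ANCOVA on the mean of the two log markers.

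**The case against.** Several stronger readings are tempting, and the article does not support them.

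- **That centre is ignored.** The CMH test of ORR is stratified by centre, and ORR covers the laboratory indicators. The mismatch with the randomisation is confined to the Wilcoxon test. The CMH test does not repair it, since it is an addition and reduces the markers to any recovery against none.
- **That the primary outcome has the weakest analysis in the plan.** The CMH test had less power still, and the logistic models name no covariates. The fair comparison is with the ANCOVA given to continuous secondary outcomes.
- **That baseline is unused.** GR and MR are percentage falls from the patient's own baseline, and NR means no improvement. Only FR is an absolute level. What is missing is baseline as a covariate.
- **That chance imbalance in disease stage drives the result, because normalisation is easier from stage III.** A check that modelled FR (one marker, 2,000 trials per setting) found a correlation of only 0.05 to 0.11 between stage imbalance and the arm difference in category score when the baseline slope was 1. Adding baseline to a centre-adjusted analysis then changed power by 0.5 to 0.7 points (87.6 against 87.1%; 61.7 against 61.0%). With slope 0.8 the correlation was -0.14 to -0.27, opposite to that argument, and adjustment gained 2 to 8 points. The effect depends on a slope the article does not give.

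Three further objections carry weight. The trial calls itself exploratory, so this is a matter of efficiency. A constant effect on the log scale favours ANCOVA by construction. The largest gains in the two-marker simulation come from a different summary (the mean of both markers); on UAER alone the gain there is 12 to 13 points. These limit the size of the claim. The direction was the same in every scenario tried.

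**Conclusion.** The point stands as one of efficiency and interpretability. The stated main test discards information in the continuous markers, leaves out the randomisation stratum and uses no baseline covariate, while the same section adopts a better method for continuous secondary outcomes. Against that method the loss is roughly 6 to 22 points of power with the same 80 patients. In addition, nothing planned for the primary outcome estimates the effect on the marker scale.

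A reader might infer that the P value is unreliable or that false positives are more likely. The calculations show otherwise: when centres differ, the unstratified test is conservative.

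Confidence is high in the direction and modest in the size. The figures rest on assumed effects, SDs, centre differences and baseline slopes. The 16-scenario simulation used one marker and did not model the either-marker rule or the renal-function condition for FR. The two-marker simulation did not model FR.

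**What to change.** Before data lock, and while the trial is still blinded:

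1. Define one continuous composite at week 16: Y = ½[ln(UAER₁₆/UAER₀) + ln(protein₁₆/protein₀)]. Analyse it by ANCOVA with arm, centre, ln UAER₀ and ln protein₀. Report exp(arm coefficient) as a geometric mean ratio with 95% CI. A single composite keeps both markers in the primary outcome and avoids needing a rule for combining two tests.
2. Report the same model for each marker separately as supportive.
3. Keep the FR/GR/MR/NR comparison as supportive, but replace the unstratified Wilcoxon with the centre-stratified van Elteren (CMH row-mean-score) test.

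No new patients or measurements are needed, and the article already uses ANCOVA elsewhere. The cost is a documented amendment to the primary analysis of a trial that was enrolling, with 20 patients randomised by March 2013 (Trial status section). The main result would also be less directly tied to the recovery categories the article adopts. The article says a formal analysis plan will be written before data locking, and the change can be recorded there as well as in the amendment.
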